### Outcome measurements

The efficacy between the two groups will be assessed by primary outcome measure: change in visual analog scale (VAS) four times (week 0, week 4, week 8, and week 12) (Table 1). The secondary outcomes measured at these four time points included (1) Neck Disability Index (NDI), (2) Self-Rating Anxiety Scale (SAS), (3) a digital pressure algometer used to assess tissue hardness, and (4) SH-105 used to assess cervical AROM (active range of motion).

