### Primary outcome measurement

#### VAS

The intensity of NCNP will be measured by a scale of 10-cm horizontal line visual analog scale (VAS) [44]. The patients will be asked “How much pain do you have this moment?”, then the patient will mark on the 10-cm horizontal line visual analog scale. Zero means “absence of pain,” while 10 represent “the worst pain.” VAS has been proved as a valid and reliable outcome measure for recording pain with ICC = 0.96 to 0.98 according to a previous study [45].

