### Secondary outcome measurements

#### NDI

The Neck Disability Index (NDI) will be used to measure the patients’ limitations in everyday life activities because of neck function [46]. It is most commonly used as a self-reported questionnaire in neck pain. It contains 10 questions, each of which comprises 6 potential answers ranging from 0 (no disability) to 5 (full disability), and the total of the NDI score varies between 0 and 50 points. The total NDI scores less than 4 indicate no disability; 5–14, mild disability; 15–24, moderate disability; 25–34, severe disability; and more than 35 points “complete disability.”

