#### SAS

The anxiety level of NCNP patients will be measured by Zung Self-Rating Anxiety Scale (SAS) [47]. Twenty questions are divided into 4 groups: cognitive, autonomic, motor, and central nervous system symptoms. Each section is scored on four levels of anxiety intensity from “1” not at all to “4” very much and with a sum score between 20 and 80. A higher total score indicates a more severe anxiety level. The total raw scores range from 20 to 80. The raw score consequently needs to be converted to an “Anxiety Index.” The primary scores should be interpreted into the Anxiety Index. The clinical interpretation of one’s level of anxiety is as follows: 20–44, normal range; 45–59, mild to moderate; 60–74, marked to severe lever; and 75–80 extreme anxiety level.

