#### Active range of motion (AROM)

Cervical active range of motion is measure by Spain ScanTM SH-105 (Ad-Or Medical Technologies Ltd., Israel). The validity and reproducibility of this measurement have been proved by many researchers [51, 52]. SH-105 is composed of a goniometer and a computer. The data will be transmitted by Bluetooth. The patient will be seated with a straight back leaning against the back of a chair. The goniometer will be placed on the center of the cranial. The researcher switches the mode and long press the “start/end” button. When hearing the prompt sounds, the patient will be asked to flex forward to the limit. The patient will be instructed to stop at the point where pain symptoms preform. The research press the “start/end” button again, and the computer will automatically record the data. Each movement (flexion-extension, lateral flexion as well as rotation) will be measured in this way three times. The mean of each movement will be recorded.

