### Statistical analysis

All statistical analyses will be performed with the SPSS software (SPSS, version 24.0, SPSS Inc., Chicago, IL, USA) by statisticians who are independent of the research team and blinded to the group allocation. Data analysis will be based on the intention-to-treat (ITT) principles. The statistical significance was accepted for values of *p* < 0.05. Participants who fail to complete the study will be treated as having no change from baseline at all times. Descriptive statistics will be used to compare demographic and baseline information and evaluate the credibility of the groups. The normality of data will be tested by the Kolmogorov-Smirnov test. Parametric statistics (Tukey test) or non-parametric statistics (Wilcoxon rank sum test) will be used for the within- and between-group according to the results of homogeneity and normality analysis. If the data does not conform to a normal distribution, a covariance analysis will be used. The efficacy will be measured at four time points. A repeated measures analysis of variance will be conducted to analyze dependent variables (from baseline and follow-up). The Bonferroni and Dunn tests will be used for multiple comparisons. The intra-group comparison (comparison between baseline and follow-up) will be tested by a two-sided paired *t* test. The difference of categorical variables (VAS, NDI, SAS, PPT, AROM) and adverse effects between the groups will be analyzed by using The chi-square test or Fisher’s exact test. All numerical data will be presented as the mean ± SD, and categorical variables will be described with percentages (%). If it is necessary, post hoc analyses will be performed. The confidence interval will be established at 95% and the significance level at 0.05.

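### The statistical analysis paragraph assigns chi-square to numeric outcomes, gives non-normal data two methods, and never says which listed analysis is primary for VAS

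*Protocol article*

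**What the plan says.** All the tests stand in one paragraph of the protocol article, under Statistical analysis. In order, it provides:

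- A Kolmogorov-Smirnov test of normality, followed by a choice based on the normality and homogeneity results: "Parametric statistics (Tukey test) or non-parametric statistics (Wilcoxon rank sum test) will be used for the within- and between-group" comparisons.
- Directly after that: "If the data does not conform to a normal distribution, a covariance analysis will be used". No covariate is named.
- A repeated-measures ANOVA of the dependent variables, with no condition attached, and Bonferroni and Dunn tests for multiple comparisons.
- A two-sided paired t test for the intra-group comparison of baseline with follow-up, also with no condition.
- "The difference of categorical variables (VAS, NDI, SAS, PPT, AROM) and adverse effects between the groups will be analyzed by using The chi-square test", with Fisher's test as the alternative.
- Numeric data shown as mean and SD, categorical data as percentages.

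The outcome sections describe the same variables as measurements. VAS is a mark on a 10-cm line. For NDI, "the total of the NDI score varies between 0 and 50 points". For SAS, "The total raw scores range from 20 to 80". AROM is read from a goniometer three times, and "The mean of each movement will be recorded". Tissue hardness is the mean of three readings.

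Outcome measurements defines the primary outcome as change in VAS, assessed at weeks 0, 4, 8 and 12. Sample size calculation uses the VAS score after 8 weeks and a formula for two means.

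**The concern.** A statistician who follows this text meets three problems.

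First, it prescribes a test for categories for the primary outcome and three secondary outcomes, all of which are numeric. NDI and SAS have published severity bands in their own sections, but VAS and AROM have none. The chi-square test on VAS therefore cannot be run until someone chooses categories, and nothing says how or when.

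Second, the rules conflict. Non-normal data go to the rank-sum test in one sentence and to covariance analysis in the next. Covariance analysis assumes roughly normal residuals, so it does not remedy non-normality. Within-group comparisons go to the rank-sum test, which treats the two samples as independent, and later to a paired t test.

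Third, none of these methods is called the primary analysis of VAS, and no primary visit is named outside the sample size section. At stake are the power of the confirmatory comparison and the reader's assurance that the reported p-value was the one planned.

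The chi-square list also contains PPT, which is neither a listed outcome nor a listed abbreviation, and omits tissue hardness, which is a listed outcome.

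**Working it through.** **Inputs.** From Sample size calculation: VAS means 5.5 (Tuina) and 4.7 (Tuina with exercise), SD 1.3, two-sided alpha 0.05, power 80%, margin 0. Assumed, because the protocol gives none: VAS cut-offs, and the correlation of baseline with week-8 VAS.

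**1. The plan's own figure.** n = 2(1.96 + 0.84)² × 1.3² / 0.8² = 41.4, rounded up to 42 per arm, as stated. Then 42 × 1.2 = 50.4, rounded up to 51, which gives the stated 102. The trial is therefore sized for a comparison of two means.

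**2. Power of that comparison.** SE = 1.3 × √(2/42) = 0.284, and 0.8/0.284 = 2.82. Normal approximation: Φ(2.82 − 1.96) = 0.805. Noncentral t with 82 degrees of freedom: 0.796. So about 80%.

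**3. Power of chi-square on dichotomised VAS.** For a cut c, the proportion below it in an arm with mean μ is Φ((c − μ)/1.3). Power is the sum of the binomial probabilities, at 42 per arm, of all 2 × 2 tables with an uncorrected chi-square above 3.84.

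| Assumed cut (cm) | Below cut, Tuina | Below cut, combined | Power |
|---|---|---|---|
| 4.0 | 0.124 | 0.295 | 50% |
| 4.5 | 0.221 | 0.439 | 58% |
| 5.1 | 0.379 | 0.621 | 65% |
| 5.5 | 0.500 | 0.731 | 61% |
| 6.0 | 0.650 | 0.841 | 54% |

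A normal approximation for two proportions gives slightly less, 49% to 60%. The 65% is a little flattering, since the uncorrected test at that cut has a type I error of about 6.4%. Fisher's exact test there has 56%.

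**4. Power of chi-square on whole-centimetre VAS.** Simulation with values rounded to the nearest centimetre gives about 36% (35% to 38% across runs). The test ignores the order of the categories and spends degrees of freedom on sparse cells.

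**5. Baseline-adjusted comparison.** SE = 1.3 × √(1 − ρ²) × √(2/42). For assumed ρ of 0.3, 0.5 and 0.7 the SE is 0.271, 0.246 and 0.203, and power at 42 per arm is 83%, 90% and 97%.

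**6. The conflicting rules side by side.**

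| Situation | One rule | Another rule |
|---|---|---|
| Between groups, non-normal | Rank-sum | Covariance analysis |
| Within group, non-normal | Rank-sum (unpaired) | Paired t test, unconditional |
| VAS between groups | Chi-square or Fisher | Repeated-measures ANOVA; Tukey or rank-sum after pre-tests |

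No sentence ranks the entries in any row.

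**The case against.** The best defence is the repeated-measures ANOVA. It is unconditional, suits numeric data, and follows directly on the statement that efficacy is measured at four time points. A reader might infer from the chi-square sentence that the primary analysis is simply wrong. The documents do not support that: a usable method is listed, but nothing makes it primary. A reader might also infer that baseline is used only when normality fails. That goes too far, because the outcome is change in VAS and the repeated-measures analysis covers baseline and follow-up.

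Other parts of the defence also stand. With two groups, Tukey's procedure gives the same p-value as the pooled t test, so naming it does no harm between groups. The between-group rank-sum test is valid, with about 77% power in simulation at 42 per arm. Its misuse on paired data affects only within-group comparisons, which do not estimate the treatment effect. PPT is probably a label slip, since tissue hardness is measured with a pressure algometer.

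The word categorical may be a slip too. Correcting it would still leave two methods for non-normal data, two for within-group data and no named primary analysis.

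One could also object that all 51 per arm will be analysed. With 51 complete cases per arm, normal approximations give 87% for the means and 57% to 69% for chi-square at the same cuts, so the gap remains. The planned no-change imputation for dropouts makes 51 complete cases optimistic anyway.

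Finally, a reader might infer an inflated type I error. If the best of five candidate week-8 tests could be reported, simulation under the null (assumed correlation 0.5) gives about 12.5% rather than 5%. The protocol does not say that results will be chosen in this way, so this is a worst case and not a property of the plan.

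**Conclusion.** The concern holds as a contradiction within the protocol and a failure to fix the primary analysis. It does not depend on anything usually left to an analysis plan, because the protocol states these rules and they conflict. Three things are established from the text alone: chi-square or Fisher is assigned to numeric outcomes, including the primary one; non-normal data and within-group data each have two incompatible methods; and no listed method is designated primary for VAS, with part of the choice left to tests on the trial data.

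The size depends on which rule is followed. Against about 80% for the comparison behind the sample size, chi-square on VAS would have about 50% to 65% if dichotomised, or about 36% on whole centimetres. These figures rest on the plan's own means and SD, on normal data and on assumed cut-offs. The gain from baseline adjustment rests wholly on assumed correlations; it is a reason to prefer that method, not evidence of an error.

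**What to change.** Reword the paragraph as follows.

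- **Primary analysis.** The between-group difference in VAS at week 8, the time point used for the sample size, with its 95% confidence interval. Obtain it from either an ANCOVA with baseline VAS as covariate or a mixed model with group, visit, group-by-visit and baseline VAS. Choose one now and use it whatever the normality test shows. Other visits are secondary.
- **Other numeric outcomes.** The same model for NDI, SAS, tissue hardness and AROM.
- **Sensitivity.** Keep the between-group rank-sum test only as a named sensitivity analysis.
- **Categorical data.** Restrict chi-square and Fisher's exact test to adverse events and truly categorical items.
- **Deletions.** Remove the rule that triggers covariance analysis by non-normality, and the within-group rank-sum test.
- **Editorial.** Replace PPT with tissue hardness.

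The cost is one paragraph and no new data. Recruitment has begun, and Quality control has protocol revisions discussed by the ethics committee and kept on record. The change should go through that route, dated, before unblinding.

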### Sample size calculation

The following two hypotheses are related to the differences between the two groups.
H0:μ1 − μ2 ≤ ΔH1:μ1 − μ2 > Δ

where μ1 is the VAS score for treating 8 weeks in the Tuina group, and μ2 is the VAS score for treating 8 weeks in the Tuina combined with Yijinjing group.

According to a previous clinical study in China [53], the mean and standard deviation of VAS in the Tuina group (*n* = 34) after the intervention was 5.5 and 1.1, respectively. The mean and standard deviation of VAS in the Tuina combined with neck exercise group (*n* = 34) after the intervention was 4.7 and 1.3, respectively.

The following formula was used to calculate the sample size in this trial:
$$ n=\frac{2{\left({z}_{\alpha /2}+{z}_{\beta}\right)}^2\times \kern0.5em {\sigma}^2}{{\left({\mu}_2-{\mu}_1-\varDelta \right)}^2} $$

$$ {\displaystyle \begin{array}{l}n=\frac{2{\left(1.96+0.84\right)}^2\times {1.3}^2}{{\left(4.7-5.5-0\right)}^2}=42\\ {}\end{array}} $$

(*α* = 0.05 *β* = 0.2, superiority design, the two-sided test, *Δ* = 0)

Considering a dropout rate of 20%, each group will require 51 cases. Therefore, a total of 102 participants should be recruited for this randomized controlled trial (RCT).

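### The efficacy outcomes, including the primary outcome VAS, are misclassified as categorical and given a chi-square or Fisher test, in conflict with the sample size and with the other tests named in the same section

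*Protocol article*

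**What the plan says.** In the protocol article, Statistical analysis, one sentence assigns a between-group test to the outcomes by name: "The difference of categorical variables (VAS, NDI, SAS, PPT, AROM) and adverse effects between the groups will be analyzed by using The chi-square test", with Fisher's exact test as the alternative. The same section says "All numerical data will be presented as the mean ± SD", and that categorical variables will be described by percentages. The label therefore decides how an outcome is reported as well as how it is tested.

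That section also provides for:
- a Tukey test or a Wilcoxon rank sum test for within- and between-group comparisons, depending on normality and homogeneity;
- a covariance analysis if the data are not normal;
- a repeated measures ANOVA over the four time points.

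None of these is named as primary for VAS.

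The outcome sections describe the measurements as follows:
- VAS, the primary outcome: "the patient will mark on the 10-cm horizontal line visual analog scale", from 0 to 10.
- Tissue hardness: the mean of three meter readings.
- AROM: for each movement, the mean of three goniometer readings.
- NDI: a total from 0 to 50, with descriptive disability bands.
- SAS: a total from 20 to 80, with descriptive anxiety bands.

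The Sample size calculation section defines its parameters as 8-week scores. For the combined arm, "μ2 is the VAS score for treating 8 weeks in the Tuina combined with Yijinjing group"; the parameter for the Tuina arm is defined likewise. The section takes a source mean and SD for the Tuina arm ("after the intervention was 5.5 and 1.1, respectively"), with 4.7 and 1.3 for the combined arm.

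**The concern.** A mark on a 10-cm line is a numeric measurement. A chi-square or Fisher test needs categories, and the article gives none for VAS, AROM or tissue hardness. The VAS threshold of 3 in the inclusion criteria governs eligibility only and is not a responder definition. NDI and SAS do have bands, but these interpret a numeric total and are not declared as the analysis variable.

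An analyst who followed the sentence literally would have to choose VAS categories that the article does not fix. If that choice were made with the data in hand, it could influence the result. Patients know their treatment and VAS is self-reported, so that freedom would be an avoidable source of doubt. A test on cut VAS also discards information, and can disagree with the comparison of means for which the trial was sized. The primary outcome would be left with two incompatible descriptions in one section: a percentage compared by chi-square, and a mean compared by a parametric or rank method.

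**Working it through.** **1. The plan's own figure.** Inputs from Sample size calculation: means 5.5 and 4.7, common SD 1.3, z-values 1.96 and 0.84, margin 0, described as "0.2, superiority design, the two-sided test". Statistical analysis agrees on the level: "The confidence interval will be established at 95% and the significance level at 0.05".

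n = 2(1.96 + 0.84)² × 1.3² / (4.7 − 5.5)² = 2 × 7.84 × 1.69 / 0.64 = 41.4, rounded up to 42 per arm.

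The figure reproduces. Power for the difference in means at 42 per arm is 80.5% by the normal formula and 79.6% by the noncentral t. With 51 per arm, the noncentral t gives 86.8%.

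**2. Each outcome against its label.**

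| Outcome | How it is measured | Categories given? |
|---|---|---|
| VAS | position on a 10-cm line | no |
| AROM | mean of three readings per movement | no |
| Tissue hardness (apparently PPT) | mean of three readings | no |
| NDI | total, 0 to 50 | descriptive bands |
| SAS | total, 20 to 80 | descriptive bands |

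PPT is not in the abbreviation list. Reading it as tissue hardness is an inference: the other four names in the bracket are the other four efficacy outcomes.

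**3. What a chi-square on cut VAS would do (illustration).** Assumptions: VAS is normal in each arm with the plan's means, and is split at a single cut c. The article gives no cut, so c is varied from 3 to 7. Two SD settings are used: 1.3 in both arms, as in the plan's formula, and 1.1 (Tuina) with 1.3 (combined), as in the source study.

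The proportions below the cut are p1 = Φ((c − 5.5)/SD1) and p2 = Φ((c − 4.7)/SD2). For c = 5.1 and SD 1.3, p1 = Φ(−0.31) = 0.379 and p2 = Φ(0.31) = 0.621. Power is the summed probability of all pairs of binomial counts for which the two-sided test (uncorrected chi-square, or Fisher) is significant at 0.05.

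| Cut | SD 1.3/1.3: chi-square, n=42 | Fisher, n=42 | chi-square, n=51 | SD 1.1/1.3: chi-square, n=42 | Fisher, n=42 | chi-square, n=51 |
|---|---|---|---|---|---|---|
| 3 | 27% | 9% | 28% | 42% | 14% | 49% |
| 4 | 50% | 41% | 57% | 72% | 63% | 79% |
| 4.5 | 58% | 49% | 66% | 74% | 66% | 82% |
| 5 | 65% | 56% | 72% | 73% | 65% | 80% |
| 5.1 | 65% | 56% | 72% | 72% | 64% | 79% |
| 6 | 54% | 45% | 62% | 44% | 35% | 51% |
| 7 | 33% | 15% | 35% | 15% | 4% | 15% |

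A normal approximation gives 60% in place of 65% at cut 5.1 (SD 1.3, 42 per arm), so these figures are good to a few points. Schemes with three to five categories, by the noncentral chi-square at 42 per arm, gave 37% to 68% over both SD settings.

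**4. Reading the table.** At the planned 42 evaluable per arm, no cut tried reaches 80%. It is reached only with all 51 per arm contributing full data, SDs of 1.1 and 1.3, and a cut of about 4.5 to 5. On the same SDs the comparison of means has 85.3% power at 42 per arm and 91.3% at 51 (noncentral t, average-variance SD √((1.1² + 1.3²)/2) = 1.204). It is therefore well ahead of the best cut in every setting.

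**The case against.** The strongest reply is that this is a drafting slip. All the efficacy outcomes, one under an undefined abbreviation, sit in a bracket after the words for categorical variables. The same section promises means and SDs for numerical data and lists methods suited to numeric outcomes. An analyst could apply the repeated measures ANOVA to VAS and never run a chi-square. That is a plausible reading, and it limits the practical harm. It does not remove the defect, because the sentence fixes a wrong test in the current text and is the only sentence in the section that ties VAS by name to a test.

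Two stronger readings are tempting, and the documents support neither.

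- A reader might infer that the 80% power claim is false or the trial undersized. The sample size section claims 80% for a difference in mean 8-week VAS only, and that calculation reproduces. It never claims 80% for a chi-square test.
- A reader might infer that chi-square is the planned primary analysis of VAS. The section names several methods for the same outcomes and ranks none of them. A separate analysis plan may do so, so the lack of ranking is not itself the complaint. The complaint is that one listed method contradicts the measurements, the sample size basis and its neighbours.

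It is also fair to say that the power figures depend on assumed cuts, normality and SDs, and that the control-arm SD of 1.1 narrows the loss at favourable cuts. They are illustrations and are labelled so.

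**Conclusion.** The point holds as a misclassification with conflicting tests. VAS, AROM and, as far as can be inferred, tissue hardness are called categorical with no categories given, and NDI and SAS are numeric totals whose bands are descriptive. Sending their between-group difference to chi-square or Fisher contradicts both the sample size basis and the mean- and rank-based methods in the same section.

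The sample size arithmetic for means is sound up to 42 per arm. The 80% does not transfer to a test on cut VAS. Under normality, with cuts from 3 to 7 and 42 per arm, chi-square power would be about 27% to 65% with SD 1.3 in both arms, and about 15% to 74% with SDs 1.1 and 1.3. It reaches about 82% at best, and only with 51 per arm, the smaller control SD and a favourable cut. This should be corrected because it concerns the primary outcome and the remedy is simple.

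**What to change.** In Statistical analysis:

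- Remove all five outcomes (VAS, NDI, SAS, PPT, AROM) from the list of categorical variables. Removing only VAS and AROM would leave the same fault in place for the others.
- State that the primary between-group comparison is the difference in mean VAS at week 8 with a 95% confidence interval, matching the sample size section.
- State that NDI, SAS, tissue hardness and AROM (each movement) are analysed as numeric outcomes. Replace PPT with the name used in the outcome section, or define it.
- Keep the chi-square or Fisher test for adverse events and truly categorical data such as sex.
- If a VAS responder analysis, or an analysis of the NDI or SAS bands, is wanted, label it supportive and fix its cut-points before unblinding.

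The cost is a few sentences of wording in the protocol or analysis plan. No new data, visits or participants are needed, and no information is lost.
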